### Study design

2.1

The PEACE trial is a prospective, multicenter, open-label, randomized controlled non-inferiority trial conducted at three hospitals in Japan. Patients will be randomly assigned in a 1:1 ratio to undergo either PFA or CBA (Fig. 1). The study aims to enroll 300 patients (150 in each group). Stratified randomization will be conducted using a random number table, based on age (<70 or ≥70 years), sex, and left atrial (LA) diameter (<40 mm or ≥40 mm), to ensure balanced allocation across these variables. Only one investigator ([name]), who will not be involved in assigning the actual interventions, will have access to the randomization sequence. The planned enrolment period is from 18 June 2025 (the IRB-approved start date) to 31 December 2027.

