### Sample size calculation

2.6

The sample size of 300 patients (150 per group) was calculated based on an assumed 12-month success rate of 54.8 % for CBA vs. 55.1 % for PulseSelect™ for PeAF as reported in previous studies [7,9]. The calculation assumed a significance level (α) of 0.05, statistical power of 80 %, and a non-inferiority margin of 1.4. For safety endpoints, a complication rate of 4.9 % was estimated for both groups. To account for potential dropouts and missing data, approximately 10 % more patients were added, resulting in 150 patients per group.

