### Statistical analysis

2.7

Time-to-event analyses will be conducted using Kaplan-Meier survival curves and compared using the log-rank test. Categorical variables will be compared using the Chi-square test or Fisher’s exact test, while continuous variables will be analyzed using the Student’s *t*-test or the Wilcoxon rank-sum test, as appropriate. A two-sided p-value of <0.05 will be considered statistically significant.

Analyses will be conducted using all available data. Missing primary outcome data will be treated as censored observations in the time-to-event analysis rather than excluded. No imputation is planned. For secondary outcomes, available-case analysis will be performed, incorporating all observed data to minimize data loss. Sensitivity analyses may be considered if the extent of missing data is substantial.

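### The log-rank test named for efficacy does not take up the three factors that randomisation is stratified by; a stratified or adjusted analysis would be a free, minor improvement

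*Protocol article*

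**What the plan says.** Section 2.1 (Study design) of the protocol article describes the allocation: "Stratified randomization will be conducted using a random number table, based on age (<70 or ≥70 years), sex, and left atrial (LA) diameter". The cut for left atrial diameter is 40 mm, and the stated purpose is "to ensure balanced allocation across these variables". Three two-level factors make 2 × 2 × 2 = 8 strata. On size, the same section says: "The study aims to enroll 300 patients (150 in each group".

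Section 2.7 (Statistical analysis) gives the time-to-event method: "Time-to-event analyses will be conducted using Kaplan-Meier survival curves and compared using the log-rank test". The same section censors missing primary outcome data in that analysis, so the log-rank comparison is the one that carries the primary efficacy endpoint. It sets the significance rule as "A two-sided p-value of <0.05 will be considered statistically significant". It mentions no strata, covariates, Cox model or hazard ratio.

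Section 2.6 (Sample size calculation) rests on an "assumed 12-month success rate of 54.8 % for CBA vs. 55.1 % for PulseSelect™ for PeAF" and a non-inferiority margin of 1.4, without saying on which scale the margin lies.

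**The concern.** Balancing the arms within strata of prognostic factors makes the treatment comparison less variable from trial to trial. A test that ignores the strata does not credit this: its standard error still allows for imbalances that the design has removed. The test then rejects less often than its nominal level and loses some power to detect a real difference.

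A second effect appears only if the result is expressed as a hazard ratio. A hazard ratio that leaves out prognostic factors lies closer to 1 than the one within strata. A non-inferiority margin applied to it is therefore applied to a slightly different quantity.

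The three factors must be known before a patient can be randomised, so they are available to the analysis at no cost.

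**Working it through.** **1. The plan's own figure.** Read the margin of 1.4 as a risk ratio on recurrence, with recurrence rates qc = 1 − 0.548 = 0.452 (cryoballoon) and qt = 1 − 0.551 = 0.449 (pulsed field):

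n = [qt(1 − qt) + 1.4² qc(1 − qc)] (z_α + z_0.80)² / (1.4 qc − qt)²

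- Bracket: 0.2474 + 1.96 × 0.2477 = 0.7329.
- Denominator: (0.6328 − 0.449)² = 0.1838² = 0.03378.
- One-sided α of 0.05: (1.645 + 0.842)² = 6.183, so n = 134.1, rounded up to 135. With 10% dropout, 135 / 0.9 = 150 per group, which is the stated figure.
- One-sided α of 0.025 on the same scale: 171, then 171 / 0.9 = 190 per group.
- Margin read as a hazard ratio: 208 events, about 462 patients before dropout, at one-sided 0.05.
- Margin read as an odds ratio: 412 per group or more.

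Of the readings tried, only the risk ratio returns 150. A risk ratio is collapsible: averaging over strata does not pull it towards 1.

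The hazard ratio implied by the design rates is ln 0.551 / ln 0.548 = 0.991.

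**2. Simulation inputs.** From the article: 300 patients, 1:1 allocation, 8 strata, about 10% dropout and 12-month success on cryoballoon of 54.8%. Assumed, because the article does not give them: block allocation within strata; 50%, 30% and 55% of patients in the higher-risk level of the three factors; and the factors' own hazard ratios, taken as none, weak (1.22/1.22/1.35), moderate (1.5/1.5/1.8) or strong (2.0/2.0/2.7). Each row below has 40,000 runs.

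**3. True within-stratum hazard ratio of 1.40** (U = unstratified, S = stratified):

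| Factor effects | Mean HR, U / S | U: model SE / empirical SE | Power to detect the difference, two-sided 5%, U / S | False non-inferiority, one-sided 2.5%, U / S | False non-inferiority, one-sided 5%, U / S |
|---|---|---|---|---|---|
| None | 1.402 / 1.402 | 0.1670 / 0.1674 = 1.00 | 52.7% / 52.3% | 2.4% / 2.4% | 4.9% / 4.9% |
| Weak | 1.396 / 1.401 | 0.1672 / 0.1647 = 1.015 | 51.7% / 52.0% | 2.5% / 2.4% | 5.0% / 4.9% |
| Moderate | 1.380 / 1.403 | 0.1674 / 0.1618 = 1.035 | 48.5% / 51.8% | 2.6% / 2.5% | 5.4% / 4.9% |
| Strong | 1.343 / 1.403 | 0.1680 / 0.1522 = 1.104 | 41.0% / 51.6% | 2.9% / 2.4% | 6.3% / 4.9% |

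**4. No true difference (hazard ratio 1), moderate effects.**

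- Two-sided rejection is 4.5% unstratified against 5.1% stratified. The Monte Carlo standard error is about √(0.05 × 0.95 / 40,000) = 0.1 point.
- The ratio of model to empirical standard error is 0.1764 / 0.1713 = 1.03 unstratified and 0.1776 / 0.1784 = 1.00 stratified.
- Both analyses give a mean hazard ratio of 1.00.
- The chance of showing a hazard ratio below 1.4 at one-sided 2.5% is 48.1% unstratified against 47.7% stratified.

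A separate simulation of the same design, with its own mild, moderate and strong effects, gave unstratified rejection of 4.9%, 4.2% and 3.0%, against about 4.6 to 5.4% stratified. There, stratifying by non-prognostic factors cost about 1 point of power.

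**5. Safety comparison.** At the stated complication rate of 4.9%, the ratio of model to empirical standard error for the unstratified risk difference is 0.99 to 1.00, even with strong assumed factor effects.

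**The case against.** The strongest objection is that the article is silent rather than wrong. It names a family of test and does not say that the test is unstratified. It condenses a fuller protocol, and a stratified version may be specified there or in an analysis plan that is not shown. This stands, and it keeps the point small: a reader may not infer that the sponsor has decided against stratifying. What remains is that section 2.7 states a method which, as written, does not use the groups named in section 2.1, and a better one is free.

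A second objection is that the size depends wholly on inputs the article does not report. This also stands. If the factors are not prognostic, or if allocation within strata does not in fact force balance, the standard error is not overstated.

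A reader might infer that the plan biases the result towards non-inferiority. The documents do not support this. No hazard ratio is planned, and the one scale found to reproduce 150 per group is not attenuated. On the hazard-ratio scale, the unadjusted and within-stratum ratios are different quantities, and they coincide when there is no difference. The larger standard error also offsets most of the shift: false non-inferiority at one-sided 2.5% is 2.4 to 2.6% unless the factor effects are strong, when it is 2.9%.

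A reader might also infer that precision is being thrown away. The stratified hazard ratio does not have a smaller standard error (0.1776 against 0.1764 at no difference). What stratification restores is the match between the stated error and the real one.

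**Conclusion.** The point holds as a free improvement of minor severity. The efficacy test is named without the stratification factors. If those factors are prognostic and balance is forced within strata, the unstratified standard error is about 1 to 4% too large for mild to moderate effects and about 10% for strong ones. Two-sided tests then run below 5%, and some power to detect a real difference is lost.

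Any shift in a hazard ratio depends on the margin being judged on that scale. A true 1.40 then reads as about 1.38 to 1.40, or 1.34 with strong effects. There is no shift at the design rates, and non-inferiority power barely moves.

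Two extensions should not be read into this. The Chi-square or Fisher comparison of complications is not materially affected at 4.9%. The absence of centre from the named tests is not shown to be an error: chance imbalance between the three hospitals is already covered by the test's error rate, and the documents give nothing from which to size a centre effect.

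**What to change.** State in section 2.7 that the primary efficacy comparison is stratified by, or adjusted for, the three randomisation factors. This means a stratified log-rank test, together with a stratified or covariate-adjusted effect estimate and its confidence interval on the scale on which the margin of 1.4 is defined. That scale has to be named for the sentence to be complete. With 300 patients in 8 strata some cells may be small, so provide for covariate adjustment in place of stratification if strata prove sparse. Keep the unstratified analysis as a sensitivity check.

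The cost is a sentence or two. No new data and no extra patients are needed, and if the factors turn out not to be prognostic the loss of power is at most about 1 point. The choice should be fixed before outcomes are seen: the trial is open-label, and leaving it open would allow a later choice between adjusted and unadjusted results.

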### Study endpoints

2.5

✔ Primary efficacy endpoint.•Freedom from any atrial arrhythmia (AF, atrial flutter, or atrial tachycardia) recurrence lasting ≥ 30 s after a 90-day blanking period for 12 months post-ablation✔ Primary safety endpoint.•Incidence of procedure-related complications within 30 days post-procedure✔ Secondary endpoints:•Changes in LA diameter•Changes in BNP/NT-proBNP levels•Early arrhythmia recurrence (within the 90-day blanking period)•Patient-reported symptoms assessed using the NRS scale

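### The change endpoints (LA diameter, BNP/NT-proBNP) would be compared without adjustment for baseline or the randomisation factors, which is valid but less precise than ANCOVA

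*Protocol article*

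**What the plan says.** Section 2.5 (Study endpoints) of the protocol article lists "Changes in LA diameter" and "Changes in BNP/NT-proBNP levels" among the secondary endpoints. Neither is tied to a time point there. Section 2.4 schedules echocardiography at 6 and 12 months.

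Section 2.7 (Statistical analysis) has one sentence on tests for data that are not time-to-event. After the part on categorical variables it continues "while continuous variables will be analyzed using" and names two options, a Student's t-test or a Wilcoxon rank-sum test, chosen as fits the data. It names no covariate. On missing data it says "For secondary outcomes, available-case analysis will be performed, incorporating all observed data to minimize data loss", and also "No imputation is planned". The significance rule is "A two-sided p-value of <0.05 will be considered statistically significant".

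Section 2.1 (Study design) stratifies randomisation by age (below 70 or not), sex and LA diameter (below 40 mm or not). Section 2.7 does not mention these factors.

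**The concern.** An endpoint defined as a change needs a baseline value for every patient analysed. Once that value is in hand, using it as a covariate costs nothing and can only help in large samples. A two-sample test on the change subtracts baseline with a fixed coefficient of 1. ANCOVA estimates the coefficient, which is below 1 whenever the correlation is imperfect and the variances are similar.

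The same holds for the randomisation factors. Stratification buys balance, but a test that leaves the factors out does not credit that balance in its standard error.

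What is at stake is the width of the confidence intervals for two secondary endpoints. There is also a conditional issue. If the arms happen to differ at baseline by an amount d, the expected difference in change scores moves by -(1-rho) times d, and ANCOVA removes this shift.

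**Working it through.** **Inputs from the article.** 150 patients per arm (section 2.1); a dropout allowance of about 10% (section 2.6), so about 150 x 0.90 = 135 per arm analysed; two-sided 0.05 (section 2.7). The article gives no SD, correlation, target difference or power for the change endpoints, so there is no stated figure to reproduce. The 80% below is only a reference level.

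**Assumptions.** Equal SD (set to 1) at baseline and follow-up, a linear relation, and a correlation rho between 0.3 and 0.9.

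**Formulas.**
- Variance of a change score: 1 + 1 - 2 rho = 2(1 - rho).
- Residual variance under ANCOVA: 1 - rho^2 = (1 - rho)(1 + rho).
- Ratio, ANCOVA to change score: (1 + rho)/2.

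Check by a second route: the squared correlation between baseline and change is (1 - rho)^2 / [2(1 - rho)] = (1 - rho)/2. Adjusting for baseline therefore leaves 1 - (1 - rho)/2 = (1 + rho)/2 of the variance.

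**Power comparison.** Take the difference that the change-score t-test detects with 80% power at 135 per arm. Its standardised size is 1.960 + 0.842 = 2.802. Under ANCOVA it becomes 2.802 / sqrt((1 + rho)/2), and power is the normal probability below that value minus 1.960. At rho = 0.5: 2.802 / 0.866 = 3.235; 3.235 - 1.960 = 1.275; power 89.9%. The number per arm that ANCOVA needs for 80% is 135 x (1 + rho)/2, rounded up.

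| Assumed rho | Change-score variance | ANCOVA variance | Ratio | ANCOVA power | ANCOVA n per arm for 80% |
|---|---|---|---|---|---|
| 0.3 | 1.40 | 0.91 | 0.65 | 93.5% | 88 |
| 0.5 | 1.00 | 0.75 | 0.75 | 89.9% | 102 |
| 0.7 | 0.60 | 0.51 | 0.85 | 86.0% | 115 |
| 0.8 | 0.40 | 0.36 | 0.90 | 84.0% | 122 |
| 0.9 | 0.20 | 0.19 | 0.95 | 82.0% | 129 |

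**Limits of the formula.** It fits LA diameter best. For natriuretic peptide it is meant for the log scale, where equal variances are more plausible. It does not carry over to raw skewed values or to the rank-sum option. The randomisation factors are not in the formula; their added effect cannot be computed from the article.

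**The case against.** The strongest reply is that nothing here is invalid. Under randomisation the unadjusted comparison of changes is unbiased, and its standard error already allows for chance imbalance. Stratifying at 40 mm limits imbalance in LA diameter, and the rank-sum option deals with skewness as far as the test goes. The endpoints are secondary and carry no power claim. The sentence is a general rule in a condensed article, and a covariate model may stand in an analysis plan that is not shown. If rho is 0.8 or 0.9, the gain is only 4 or 2 power points.

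Most of this stands and sets the weight of the point. It does not remove it: the article does not leave the method open but names the tests, and an analysis plan with ANCOVA would depart from the published text.

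Three stronger readings are tempting, and the article does not support them.
- *The baseline is ignored, or the comparison is confounded.* A change score does use baseline, by subtraction, only less efficiently.
- *BNP and NT-proBNP are pooled on one scale.* The slash in section 2.5 can mean either assay, or both analysed apart. Nothing says that values are combined or that the three hospitals use different assays.
- *The 6- and 12-month visits are tested separately and partial data are thrown away.* Section 2.7 does not describe tests by visit, and it states the aim of using all observed data.

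**Conclusion.** The point holds as one of efficiency. The stated tests compare the change endpoints without adjustment for baseline or for the factors used in randomisation, and a better method is available from data that the trial must collect anyway. The ANCOVA variance is 65% to 95% of the change-score variance for assumed correlations of 0.3 to 0.9. At the reference difference this is a gain of about 2 to 13.5 power points. The size rests on equal variances and on a correlation that the article does not give; it is modest if the correlation is high. Validity is not in question, and no conclusion on the primary efficacy or safety endpoint depends on it.

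**What to change.** In section 2.7 (and in the analysis plan, if it follows the article), add:
- Change in LA diameter is analysed by ANCOVA, or by a mixed model over the 6- and 12-month echocardiograms, with the baseline value (continuous) and the randomisation factors (age group, sex, LA diameter group) as covariates. State which visit gives the main contrast.
- Natriuretic peptide is analysed on the log scale with log baseline as covariate and reported as a ratio of geometric means. If both assays are used, BNP and NT-proBNP are kept separate or assay type is added as a covariate, with baseline and follow-up of a patient from the same assay.

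The cost is a few sentences. It needs no extra patients or visits; if both assays are in use, the assay type must be recorded with each value. The change should be made before outcome data are examined by arm.

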### Ethics

2.8

This study will be conducted in accordance with the principles of the Declaration of Helsinki. This protocol has been approved by the Ethics Committee of Kitasato University Hospital (Approval No. C24-157) and registered with both ClinicalTrials.gov (NCT07064616) and the University Hospital Medical Information Network (UMIN000057896). Written informed consent will be obtained from all participants prior to enrolment. The results will be submitted for publication in peer-reviewed journals and presented at relevant scientific conferences.

## Discussion

3

The PEACE trial is the first randomized controlled trial to evaluate PFA using the PulseSelect™ in comparison with CBA using the Arctic Front Advance™ for patients with PeAF. The trial aims to provide critical evidence on whether PFA can achieve comparable efficacy to CBA while offering a reduced risk of complications.

Pulsed-field ablation was introduced into clinical practice in 2019. Its most distinctive feature is the tissue-selectivity of the pulsed-field energy [8]. PV stenosis is one of the serious complications associated with thermal energy-based catheter ablation procedures [11]. As of 2025, no cases of PV stenosis have been reported with PFA [12]. Furthermore, collateral damage such as esophageal ulcers, gastric hypomotility, and permanent phrenic nerve injury has not been observed. Although these complications have decreased even with the use of CBA, fatal events have still been reported. On the other hand, complications specific to PFA, such as hemolysis, hemolysis-related renal dysfunction [13], and coronary spasm [14], have been reported. This study will specifically assess these complications in comparison with those associated with thermal energy-based ablation systems. In this study, we will assess the incidence of hemolysis and related renal insufficiency via laboratory parameters (hemoglobin, creatine kinase, serum creatinine, and urinary hemoglobin) at baseline, day 1, 6, and 12 months. Moreover, the long-term efficacy of the PFA system remains insufficiently established, particularly in patients with PeAF. While thermal ablation typically produces an irreversible lesion, electroporation induced by pulsed-field energy has been reported to be partially reversible [15]. It remains challenging to determine whether the pulsed-field applications reliably create irreversible lesions, as local potential often disappears temporarily, regardless of the reversibility of the electroporation. Therefore, the durability of the created lesion following PFA will be a critical outcome of interest. A retrospective study comparing the recurrence of AF after three different energy sources for PeAF demonstrated [16] that penta-spline PFA and Arctic Front Advance™ cryoablation achieved compatible outcomes, outperforming radiofrequency catheter ablation.

This study has some limitations. Because it is an open-label design, blinding of patients and operators to the modality and outcomes is not feasible, which may introduce bias. Nonetheless, recurrence of atrial tachyarrhythmia will be adjudicated using objective evidence from ECGs or one-week Holter monitoring, which is expected to minimize its influence on the results.

The PEACE trial, as a prospective, randomized controlled trial, will evaluate the efficacy of PFA in comparison with CBA, which has demonstrated high lesion durability. This trial is expected to provide clinically meaningful evidence regarding the selection of energy sources for the ablation in patients with PeAF.

## Conclusion

4

The PEACE trial is expected to provide pivotal data on the efficacy and safety of PFA using the PulseSelect™ compared with CBA in patients with PeAF. The findings will help inform future clinical practice and guide optimal energy source selection for catheter ablation in AF.

## Ethics approval statement

This study was approved by the ethics board at Kitasato University Hospital (No. C24-157).

**Clinical trial registration:** NCT07064616, UMIN000057896.

## Data Availability

Not applicable.
